### Plans to give access to the full protocol, participant level-data and statistical code {31c}

The principal investigator will provide access to the anonymized data upon reasonable request.

### Oversight and monitoring

#### Composition of the coordinating centre and trial steering committee {5d}

Principal investigator and members of the research team will oversee and responsible for monitoring the research.

### Composition of the data monitoring committee, its role and reporting structure {21a}

No harm to participants is expected.

### Adverse event reporting and harms {22}

In this study, no harm or adverse events are anticipated. However, in case of any adverse events, principal investigator will take appropriate actions to address them.

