### Eligibility criteria {10}

Criteria for inclusion in the study will be: (a) age between 18–65; (b) diagnosis of cancer; and (c) a score above 26 on the cognitive MOCA test [24]. Volunteers with orthopedic injuries that in the opinion of the attending physician prevent their participation in physical exercise, or individuals engaged in other physical activity on a regular basis, will not be eligible to participate in the present study. Recruitment of colorectal cancer patients and breast cancer patients for the study will be within 3 months of cessation of chemotherapy treatment.

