### Intervention description {11a}

(A) Water exercise group where the Ai-Chi technique was selected as the exercise method of choice. The activity will take place in a hydrotherapy pool approved by the Ministry of Health and will be led by a hydrotherapist who has been trained in Ai-Chi.(B) Land exercise group who will perform the same Ai-Chi movements on land in order to standardize the groups. The activity will take place in a hall and will be led by a physiotherapist who has been trained to teach Ai-Chi on land.(C) Control group who will not perform additional physical activity or receive any extra treatments. In accordance with the recommendations for physical activity among cancer patients and the guidance of the hydrotherapy organization for hot water activities, the exercise program will be scheduled for 30 min twice a week for 8 weeks. The physical activities will take place in groups of 5 participants per group.

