### Strategies to improve adherence to interventions {11c}

The therapists of intervention groups will encourage the participants to attend intervention sessions. If a participant is absent from a session, a research member will contact personally.

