### Provisions for post-trial care {30}

No potential harm is expected from this study.

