### Sample size {14}

One hundred and fifty cancer patients aged 18–65 years (stage III colon cancer patients and breast cancer patients with lymph node involvement) will be recruited via advertisements in Hadassah Medical Center and Tal Aviv University. The sample size is based on data from the WHO Disability Assessment Schedule (WHODAS 2.0), which has been used internationally to assess function and disability among a healthy population versus an unhealthy population [26]. The expected difference in the questionnaire scores between the two groups is 15 points and the average standard deviation is 15.08. The sample calculation includes a type 1 error of alpha equal to 0.05 with a power of 80%. According to this calculation, 16 participants are needed in each of the three study groups. Because we anticipate the withdrawal of some of the participants and because of the clinical condition of all participants, a number of 50 participants per group was selected.

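### Adverse events are acted on only as they come to light, while staff contact differs by arm, so most harms could not be compared fairly between water, land and control

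*Protocol article*

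**What the plan says.** The protocol article, under Adverse event reporting and harms {22}, opens with a premise, "In this study, no harm or adverse events are anticipated", and follows it with one rule: "in case of any adverse events, principal investigator will take appropriate actions to address them". The premise recurs under the data monitoring committee item {21a}, "No harm to participants is expected", and under post-trial care {30}, "No potential harm is expected from this study".

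The primary outcomes are employment barriers with return to work and working hours, WHODAS 2.0, and EORTC QLQ-C30. The secondary outcomes are the Piper Fatigue Scale and the CIPN20 neuropathy questionnaire. None is an adverse-event outcome.

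The two exercise arms meet twice a week for 8 weeks in groups of 5 led by a therapist (Intervention description {11a}). Under Strategies to improve adherence {11c}, "If a participant is absent from a session, a research member will contact personally". The control arm has no sessions. All three arms share the assessments at baseline (T0), at the end of the intervention (T1) and at 3, 12 and 24 months after it (T2 to T4), with a phone interview if a visit is missed. Participants and caregivers are not blinded.

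**The concern.** The harms section takes a position; it is not simply silent. It expects no events and acts on those that become known. What becomes known under such a rule depends on who is in contact with staff, and during the intervention that differs by arm by design. The harms results could then be sparse because no outcome captures events, or show an excess in the exercise arms that partly reflects closer observation. Neither would be a sound basis for the policy use foreseen in the Discussion, where the programme is presented as a convenient, non-invasive option.

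The premise also sits uneasily with other parts of the article. Eligibility {10} excludes "Volunteers with orthopedic injuries that in the opinion of the attending physician prevent their participation in physical exercise". The session schedule draws on "the guidance of the hydrotherapy organization for hot water activities". The sample size is raised from 16 to 50 per group "Because we anticipate the withdrawal of some of the participants and because of the clinical condition of all participants". These suggest that some risk was foreseen, although none says that harm from the intervention is expected.

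**Working it through.** **Plan's own figure.** The article gives no event rate, detection rate or harms calculation, so there is nothing on this point to reproduce. Its only sample-size figure, 16 per group on WHODAS 2.0, does reproduce: 2 × (15.08 × (1.960 + 0.842) / 15)² = 15.87, rounded up to 16. The point does not depend on it. The group size used below is the planned 50 per arm.

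**Contact by arm** (Intervention description {11a}, Trial design {8}, Outcomes {12}):

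| | Each exercise arm | Control |
|---|---|---|
| Supervised sessions before T1 | up to 2 × 8 = 16 | 0 |
| Contact after a missed session | yes | not applicable |
| Shared assessments, T1 to T4 | 4 | 4 |

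Over both exercise arms this is up to 16 × 50 × 2 = 1,600 participant-sessions, against none in controls. The imbalance lies in the 8 weeks of the programme. From T1 onward the scheduled assessments are the same.

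**Effect on observed events.** Observed events = n × true risk × share noticed. With equal true risk and equal n, the apparent risk ratio is (share noticed in exercise arm) / (share noticed in control), whatever the true risk. The shares are assumptions:

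- 90% against 30%: 0.90 / 0.30 = 3.0
- 90% against 50%: 0.90 / 0.50 = 1.8
- 90% against 90% (equal questioning): 1.0

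In counts, with n = 50 and an assumed true risk of 10%:

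- exercise arm: 50 × 0.10 × 0.90 = 4.5
- control at 30%: 50 × 0.10 × 0.30 = 1.5
- control at 50%: 50 × 0.10 × 0.50 = 2.5

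**What equal questioning can deliver.**

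- If an event type is seen in 0 of 50, the one-sided 95% upper limit for its rate is 1 − 0.05^(1/50) = 0.058, or 5.8%.
- Power to distinguish an assumed 5% from 15% with 50 per arm is about 38%.

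Equal questioning therefore removes the bias from unequal contact, but leaves the comparison imprecise.

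**The case against.** The strongest reply is that this is a condensed article. Adverse-event forms, reporting routes and by-arm tables usually sit in the full protocol, which is not shown. The harms section does not forbid recording events, the team meets weekly to monitor the study {23}, a therapist leads each group of 5, and comparing harms is not among the objectives. It is true that a fuller document may contain a collection procedure. But the article states both a rule and its rationale under the harms heading, and that rule, followed as written, makes detection depend on contact.

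Several stronger readings are tempting, and the article does not support them:

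- **That other sections contradict the no-harm premise.** The orthopedic exclusion and the hot-water guidance are precautions compatible with low residual risk. The sample-size remark about clinical condition stands beside anticipated withdrawal and says nothing about exercise injury. The fatigue and neuropathy in the Background are attributed to cancer treatment. This is tension, not contradiction.
- **That harm cannot be compared at all.** Controls share T1 to T4, and worsening fatigue, neuropathy, function and quality of life are measured alike in all arms.
- **That an injured absentee is recorded as an attendance failure.** The discontinuation criteria {11b} count missed sessions but do not say how reasons are recorded, and an absence does trigger a personal contact.
- **That pool injuries would reach the principal investigator only by chance.** No formal route is stated, but sessions are supervised and the team meets weekly.
- **That a particular false excess can be predicted.** A more extreme assumed split, 80% against 20%, would show 50 × 0.10 × 0.80 = 4 events against 50 × 0.10 × 0.20 = 1. Nothing in the article favours that pair over milder ones.

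**Conclusion.** The point holds in a limited form. The article sets a purely reactive rule for adverse events on a premise that none are anticipated, lists no outcome that captures them, and has up to 16 supervised sessions per exercise participant against none per control before T1. That spontaneously noticed events would tend to come from the exercise arms is an inference from the contact schedule, not something the article states. Falls, injuries and other events outside the shared questionnaires could not be compared fairly between arms.

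The size of the distortion is not known. The apparent ratio of 1.8 to 3.0 rests on equal true risks and on assumed detection of 90% against 50% to 30%; the article gives no figures from which to narrow this. The conclusion concerns the article's text and would ease if the full protocol already asks about adverse events in the same way in every arm.

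**What to change.** Replace the reactive rule under Adverse event reporting and harms {22} as follows:

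- Ask the same short set of questions (falls, injuries, new or worsened symptoms, unplanned medical contact) in all three arms at T1, T2, T3 and T4, at the existing visits or phone interviews. Report events by arm as randomised.
- Log incidents observed at sessions separately and keep them out of the between-arm comparison, since controls have no sessions.
- Record the reason for absence (illness or injury, or other) on the call already made under {11c}.
- Have therapists and the data collector bring any event to the weekly team meeting under {23}.
- Remove the expectation of no harm as the basis for the harms section.

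The cost is slightly longer visits, one extra table, and an amendment through the two ethics committees named under {25}. No new staff or visits are needed. Two limits remain: answers are self-reported by unblinded participants, so equal questioning removes unequal contact but not every reporting difference; and with about 50 per arm the results should be presented as description.

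If the full protocol already does this, it is enough to state it in {22} and delete the premise.

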### Frequency and plans for auditing trial conduct {23}

The research team meets weekly to monitor the study and its procedures.

### Plans for communicating important protocol amendments to relevant parties (e.g. trial participants, ethical committees) {25}

All changes in the protocol must be approved by the Tel-Aviv University Ethics Committee and the Helsinki Committee of Hadassah Medical Organization, Israel. If any changes to the protocol are required during this trial, a new protocol will be designed and submitted for approval before implementation.

### Dissemination plans {31a}

Results of this study will be disseminated in: (1) scientific conferences, and (2) peer-reviewed indexed journals.

## Discussion

The popularity of exercise is increasing among cancer patients. Previous studies have reported the beneficial effects of exercise on exhaustion and fatigue [10], neuropathy [11], and overall quality of life [12] among cancer patients. However, few studies have specifically examined the impact of aquatic exercises [20, 21]. The existing studies suffer from low methodological quality, making it difficult to draw definitive conclusions regarding the true therapeutic effect of aquatic exercise.

This study aims to address this gap by conducting the first randomized controlled trial to investigate the effects of an exercise program conducted in water, compared to an identical program on-land, as well as a non-interventional exercise program, on cancer patients. The study will assess the levels of exhaustion, fatigue, and neuropathy, which are symptoms that significantly impact patients' daily activities, quality of life, and ability to return to work. By restoring the ability of cancer patients to fully engage in daily activities, it is expected that this study will promote the potential for their earlier return to work, ultimately reducing their reliance on social and economic support. The implications of this study on socio-economic policies are significant, as the results may offer a convenient, cost-effective, and non-invasive intervention program that can alleviate exhaustion, fatigue, and neuropathy, leading to improved quality of life and increased participation in daily activities, including a faster return to work. An expedited return to work and reduced dependence on social services would have both personal and public importance.

## Trial status

This is the first version of the protocol (registered 22 June 2022). The recruitment process started on April 01, 2023, and is expected to be completed in August 2027.

## Abbreviations

WHODAS 2.0: The World Health Organization Disability Assessment Schedule
EORTC QLQ-C30: The European Organization for Research and Treatment of Cancer core quality of life questionnaire
EORTCOLO QLQ-CIPN20: The European Organization for Research and Treatment of Cancer Quality of Life Questionnaire–Chemotherapy-Induced Peripheral Neuropathy 20-item scale
